The sound and illuminance levels are recorded from day 1 to day 6 using the integrated sound pressure level meter and the illuminance level meter. Continuous equivalent sound pressure levels (Leq) in ‘A’ weighted decibels and peak sound pressure levels (Lpeak) in ‘C’ weighted decibels are logged every second. The illuminance level (in lux) is recorded once per minute using a sensor placed close to the patient’s head. The bedside nurse should be asked to log an event whenever the patient received treatment or care. The event log will contain the following items: clinical assessment, tracheal suctioning, pressure area care, physiotherapy, mouth or eye care, blood test (sampling), washing, non-invasive blood pressure, eating and drinking, dressing, pain, line insertion and X-ray. Drug records are compiled daily for drugs that are known to adversely affect sleep or melatonin pharmacokinetics.

At the time of the ICU discharge, patients’ data and vital statuses, lengths of mechanical ventilation, the number of days of antibiotics use, the number of delirium-free days, the length of the ICU stay and ICU mortality will be recorded.

To investigate the enteral absorption and metabolism of orally administered melatonin in critically ill patients during their ICU stay and to evaluate the serum melatonin levels and their circadian variations in these patients, the melatonin levels are measured in blood samples taken on days 1 and 2 (before the intervention) and days 5 and 6 (four days after the intervention) at 20:45 (before administration), 9:10 pm, 9:30 pm, 00:00 am, 3:00 am, 6:00 am, 2:00 pm and 8:00 pm in 20 patients from each group. The plasma levels of norepinephrine and cortisol are also measured at the same time points. In addition, plasma levels of SOD, MDA, catalase (CAT), IL-6 and IL-8 are measured at 07:00 am on days 2 and 6.

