### Current sample size justification

Primarily, we expect an increase in the time of the patient’s night sleep after melatonin administration in ICU patients with sleep deprivation. Based on retrospective data from our institution in the same population (mean TST from the nightly sleep was 3.5 hours with a SD of 1.8 hours). A 20% (0.7 hour) difference in the nightly sleep time between the two study arms is considered clinically relevant and likely to influence practice. Using the Power Analysis and Sample Size for Windows software (PASS2000, NCSS, Kaysville, Utah, United States), we will need to study 82 experimental subjects and 82 control subjects to be able to reject the null hypothesis that the population means of the experimental and control groups are equal with a probability (power) of 0.8 by the two-side paired *t*-test. The Type I error probability with testing this null hypothesis is 0.05. Assuming a dropout rate of 20%, 99 patients per group will be recruited.

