### Statistical analysis

All analyses will be performed according to the intention-to-treat principle, that is, all randomized patients will be analysed in the groups to which they were originally allocated and will be blinded to treatment assignment. Baseline patient characteristics will be compared and described using the appropriate statistics. Categorical variables will be presented as the numbers and percentages and will be analyzed by the *χ*^2^- tests or Fisher’s exact tests, or when appropriate, as relative risks. Continuous variables will be checked for normal distribution by the Kolmogorov-Smirnov test. Normally distributed variables will be expressed by their mean and standard deviation; non-normally distributed variables will be expressed by their medians and 95% confidence levels. Comparisons of continuous variables will be performed using Student’s *t*-test for normally distributed variables and the Mann-Whitney U test for non-normally distributed variables. Appropriate (linear, logistic, or Poisson) regression will be generated for the identification of the determinants of outcomes and for the correction of baseline covariates.

One-way repeated measures analysis of variance (ANOVA) were used to determine differences in the sleep variables, the subjective sleep quality, anxiety levels and plasma levels of melatonin, cortisol and norepinephrine. Twenty-eight day mortality will be analysed according to the Kaplan-Meier method and the results will be compared with the log-rank test hazard ratios and reported with 95% confidence limits. The number of delirium-free days, ventilation-free days and antibiotics-free days will be tested by Student’s *t*-test for normally distributed data and the Mann-Whitney U-test for non-normally distributed data. The differences in adverse events between the intervention and placebo groups are used for safety analyses. All tests of significance will be at the 5% significance level and two-sided. All of the data in this trial will be assessed with SPSS Statistics version 20.0 (SPSS, Chicago, Illinois, United States). The main analysis will be fully specified before unmasking.

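### As named, repeated-measures ANOVA uses only patients with every planned value, which fits poorly with analysing all randomised patients when 20% dropout is assumed

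*Protocol article*

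**What the plan says.** The Statistical analysis section of the protocol article sets the population by intention to treat: "all randomized patients will be analysed in the groups to which they were originally allocated". The next paragraph names the method: "One-way repeated measures analysis of variance (ANOVA) were used to determine differences in the sleep variables". The same sentence applies it to subjective sleep quality, anxiety and "plasma levels of melatonin, cortisol and norepinephrine". The article names neither a mixed model nor imputation.

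The repeated values are set out under Data collection and management:

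- **PSG:** two 24-hour recordings, from day 1 to day 2 and from day 5 to day 6, both starting at 9:00 pm.
- **Richards Campbell Sleep Questionnaire (RCSQ) and anxiety scale (VAS-A):** 9:00 am on day 2 and on day 6.
- **Melatonin, cortisol and norepinephrine:** two sampling periods, one before treatment and one on days 5 and 6. Each has eight draws, "at 20:45 (before administration), 9:10 pm, 9:30 pm, 00:00 am, 3:00 am, 6:00 am, 2:00 pm and 8:00 pm", in 20 patients per group.

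The sample size section sets recruitment at 99 per group, "Assuming a dropout rate of 20" per cent. The section on the end of participation lists refusal, a new exclusion criterion, a severe adverse event, worsening, ICU discharge and death as reasons for leaving.

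**The concern.** Classical repeated-measures ANOVA needs a full row of values for each patient. A patient with one gap is left out of that analysis together with all of the values that were obtained. Adding an arm factor does not change this, so the point is separate from whether a one-way model compares the arms at all.

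The plan therefore combines a method that keeps complete rows, a promise to analyse everyone randomised, and an expectation that a fifth of patients will be lost. Two things are at stake:

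- **Lost information.** Observed values are discarded. The hormone subset is most exposed: it is small and has many samples per patient.
- **Possible bias.** Patients who leave because they worsen or die, or because they are discharged, are unlikely to be a random sample of those enrolled.

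**Working it through.** **1. The plan's own dropout figure.** Inputs are 82 per group and 20% dropout, from the sample size section.

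- 82 × (1 + 0.20) = 98.4, rounded up to 99 per group, or 198 in all. This reproduces the stated figure.
- Applying the 20% to those recruited: 99 × 0.80 = 79.2 per group, and 198 × 0.80 = 158.4.

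If every dropout lacks the second occasion, about 158 of 198 have both PSGs and can enter the ANOVA. The number is higher if some dropouts are assessed early, and lower if recordings fail in patients who stay.

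**2. Hormone subset.** There are 8 draws × 2 periods = 16 samples per patient, in 2 × 20 = 40 patients. The article gives no rate of missed samples, so the rate p is an assumption, shown as a range, with misses taken as independent. The share of patients with a full row of k samples is (1 − p)^k.

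| Assumed p | k = 16, one ANOVA over both periods | k = 8, each profile alone |
|---|---|---|
| 1% | 0.99^16 = 0.851, 34 of 40 | 0.99^8 = 0.923, 37 of 40 |
| 2% | 0.98^16 = 0.724, 29 of 40 | 0.98^8 = 0.851, 34 of 40 |
| 5% | 0.95^16 = 0.440, 18 of 40 | 0.95^8 = 0.663, 27 of 40 |

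These are shares before dropout. If the trial-wide 20% also applied to the subset, which the article does not say, the k = 16 column would become 20 × 0.8 × 0.851 = 13.6, 20 × 0.8 × 0.724 = 11.6 and 20 × 0.8 × 0.440 = 7.0 patients per group.

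**3. The complete-case property.** A simulated set of 40 patients by 16 time points with one value removed was given to a standard repeated-measures ANOVA routine (statsmodels, not SPSS). It refused the data as unbalanced.

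**4. What a mixed model would recover for sleep.** Take 79 patients per arm with both occasions and 20 with baseline only, equal variances, and correlation ρ between occasions. For the arm difference in change:

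- The complete-case variance per arm is proportional to 2(1 − ρ)/79.
- The mixed-model variance, with separate baseline means, is proportional to (1 − ρ²)/79 + (1 − ρ)²/99.
- The relative reduction is therefore (1 − ρ)/2 × 20/99.

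At an assumed ρ = 0.3 this is 0.35 × 0.202 = 7%; at ρ = 0.7 it is 0.15 × 0.202 = 3%. If the two arms share one baseline mean, baseline-only patients add nothing to the arm contrast. The precision gain for sleep is small.

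**The case against.** The strongest reply is that missing-data rules belong in an analysis plan that is not shown. The article says that the main analysis will be fully specified before unmasking, and nothing in it rules out imputation ahead of the ANOVA. This stands as far as it goes: one may not conclude that the method makes an all-randomised analysis impossible. What remains is that the article names a technique, and an analysis plan that follows it to the letter inherits the mismatch.

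Three stronger readings are tempting, and the documents do not support them.

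- **That missed blood samples break the intention-to-treat promise.** The serial samples concern 40 of 198 patients by design, so they never cover everyone randomised. A missed value affects only the hormone concerned, and the article does not say that all 16 points enter one ANOVA.
- **That a patient with a failed baseline PSG is lost from the primary comparison.** Such a patient is lost from the ANOVA. But Data collection and management limits analyses to the fourth day, the sample size section rests on a t-test of night sleep between arms, and Statistical analysis also lists Student's t-test and the Mann-Whitney test. A between-arm comparison at day 5-6 needs no baseline recording.
- **That every dropout lacks the second PSG.** Under Trial interventions, some patients who stop the study drug stay in the study and have end-of-treatment assessments at once. The 158 is the case in which none of the 20% contributes a second recording.

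It is also fair to say that the plainest conflict with intention to treat lies elsewhere. The section on ethical aspects and informed consent says that withdrawn patients' data are not analysed. A change of model does not cure that.

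**Conclusion.** The point holds as a poor fit between a named method, the stated population and the assumed dropout, and it is worth correcting. As named, the ANOVA would analyse about 158 of 198 patients for sleep, RCSQ and VAS-A if all dropouts lack the second occasion, and would also discard valid day 5-6 values where the baseline is missing. In the hormone subset it would keep 85%, 72% or 44% of patients per hormone at assumed miss rates of 1%, 2% or 5% if all 16 samples are modelled together, and 92%, 85% or 66% if each profile is modelled alone. Those shares rest on the assumed rates and on independent misses, and exclude dropout.

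The practical gain from changing the method is mainly in the hormone subset. For sleep it is modest, since no model observes a day 5-6 outcome that was never recorded.

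**What to change.** Replace the repeated-measures ANOVA by a linear mixed model with arm, time and arm-by-time, fitted to all available values in the randomised groups.

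- **Hormones:** use all available samples of every sampled patient, with a covariance structure that allows for the unequal intervals, which run from 20 minutes (9:10 to 9:30 pm) to 8 hours (6:00 am to 2:00 pm).
- **PSG, RCSQ and VAS-A:** use two occasions, baseline and day 5-6, so that a patient with only one still contributes.

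State the missing-at-random assumption and the covariance structure. Reconcile the intention-to-treat sentence with the exclusion of withdrawn patients' data, which the model does not settle.

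The cost is wording only, with no change to data collection, and it can be done while the data are blinded. The downside is that the two assumptions must be stated and defended.

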### Dissemination policy

According to the Standard Protocol Items: Recommendations for Interventional Trials (SPIRIT) guidelines, the authors declare that data that break the blinding will not be presented prior to the release of the mainline results. Breaking of the blinding will occur at the end of the study. A clinical article will be written on the primary (and secondary) outcomes of the study and the results will be disseminated regardless of the magnitude or the direction of effect. The present trial is not industry-initiated. As such, there are no publication restrictions imposed by sponsors.

In addition, a full study report, an anonymized participant-level dataset and the statistical code for generating the results will be made publicly available no later than three years after the termination of the study for sharing purposes.

## Discussion

This study is the first large sample size, prospective double-blind, ramdomized, placebo-controlled trial powered to test the hypothesis whether melatonin improve the sleep quality in ICU patients. Previous researches mainly had small sample size, and they did not use the PSG, the gold standard for assessing sleep, to evaluate sleep quality and ignored the importance of monitoring the all-day sleep. Therefore, our study is also the first to use 24-hour PSG as monitoring tools to evaluate the effect of melatonin on sleep quality in ICU patient. However, the authors acknowledge the limitation of only including patients who pass the weaning screening and are therefore ready to be weaned from mechanical ventilation, and not including who are administered medication for sedation and analgesia. Therefore, the enrolled patients might be inclined to have the longer length of ICU stay or be relative milder case. So we can not investigate most of ICU patients who are just admitted to ICU or treated intubation and mechanical ventilation.

Even so, significant differences in the safety and/or efficacy endpoints will provide important evidence for improving ICU patient sleep quality. A neutral result will also provide important insight, as this would mean that more studies are needed to evaluate the safety and efficacy of melatonin for ICU sleep deprivation.

## Trial status

The study has been initiated as planned in February 2014. One interim analysis advised continuation of the trial. The study will be completed in February 2015.

## Abbreviations

APACHE II: Acute Physiology and Chronic Health Evaluation II score
BP: Blood pressure
BPS: Behavioural pain scale
CAM-ICU: The confusion assessment method for the intensive care unit
CAT: Catalase
COPD: Chronic obstructive pulmonary disease
ECG: Electrocardiograph
EEG: Electroencephalograph
EMG: Electromyograph
EOG: Electrooculograph
GCS: Glasgow coma scale
HR: Heart rate
ICU: Intensive care unit
IL: Interleukin
MDA: Malonaldehyde
NREM: None rapid eye movement
NSAIDs: Non-steroidal anti-inflammatory drugs
PSG: Polysomnography
RASS: Richmond agitation sedation scale
RCSQ: Richards Campbell sleep questionnaire
REM: Rapid eye movement
RR: Respiratory rate
SCN: Suprachiasmatic nuclei
SOD: Superoxide dismutase
SOFA: Sequential organ failure assessment
SpO2: Peripheral oxygen saturation
TST: Total sleep time
SWS: Slow wave sleep
VAS-A: Visual analogue scale-anxiety
VNR: Verbal numeric rating.
